## Abstract

**Background:**

Despite good results of primary total knee arthroplasty (TKA), the number of revision total knee arthroplasties (rTKAs) is rising. Proper implant position is essential, since malposition leads to worse clinical outcome. In rTKA most anatomical landmarks have disappeared because of extensive bone loss, making it more difficult to adequately implant the knee prosthesis. In primary TKA, computer-assisted surgery (CAS) leads to better prosthetic alignment than mechanical navigation guides. Literature about the use of CAS in rTKA is scarce though, and the effect on rotational prosthetic alignment has not been investigated yet. Hence the primary objective of this study is to compare rotational prosthetic alignment when using CAS in rTKA compared to a mechanical navigation guide. Secondary objectives are to compare prosthetic alignment in the coronal and sagittal planes. It is hypothesized that CAS leads to better rotational, coronal and sagittal prosthetic alignment when used during rTKA.

**Methods/Design:**

A prospective clinical intervention study with use of a historical control group will be conducted. Forty-four patients with a minimum age of 18 to be admitted for CAS-rTKA between September 2012 and September 2015 will be included in the intervention group. Forty-four patients with a minimum age of 18 who underwent rTKA with the use of a mechanical navigation guide between January 2002 and April 2012 will form the historical control group. Both groups will be matched according to gender and type of revision prosthesis. Rotational prosthesis alignment will be evaluated using a CT-scan of the knee joint.

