## Methods/Design

### Study design

A prospective clinical intervention study with use of a historical control group will be conducted. In the prospective intervention group patients will undergo rTKA using CAS. These surgeries will take place between September 2012 and September 2015. The historical control group will consist of patients who underwent rTKA between January 2002 and April 2012. The intervention and control groups will be matched according to gender and type of revision prosthesis. The study design, procedures and informed consent are approved by the Medical Ethics Committee of University Medical Center Groningen (UMCG).

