### Sample size

The hypothesis is that the use of CAS leads to fewer outliers in prosthetic alignment compared to the use of mechanical alignment guides during rTKA. Primary outcome measure will be rotational prosthetic alignment. When using the conventional operation technique, around 25% of the knees is considered a radiological outlier. Therefore, a P2 value of 0.75 was chosen [21,36]. Previous research has shown that the use of CAS in TKA decreases the number of outliers by 17-30% [21,37,38]. When a 20% decrease in outliers is expected in the CAS group compared to the control group with P1 = 0.95, P2 = 0.75, power = 80% and alpha = 0.05, 44 patients per group are needed.

Since 2008 a total of amount of 21-30 rTKAs have been performed each year at UMCG, and an increase is expected. As a result of that, the possibility is expected of including 44 patients in the intervention group between September 2012 and September 2015. Inclusion of 44 patients in the historical control group is not expected to be a problem, as 165 rTKAs were performed between January 2002 and April 2012.

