### Statistical analysis

All statistical analyses will be performed using the PASW software package (version 19, SPSS, Chicago, USA). Descriptive statistics will be used to describe the main characteristics of both research groups. Differences in rotational, coronal and sagittal alignment between the groups will be determined by using the nonparametric Mann-Whitney U-test for independent samples. For the clinical parameters, t-tests will be used for continuous values or the Mann-Whitney U-test when the variables are not normally distributed. A Chi-square test and a Fisher’s Exact test will be used for dichotomous values. For all test procedures, a p-value of < .05 will be considered to indicate statistical significance.

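### The groups are matched on gender and prosthesis type, but every named test ignores both factors; this is conservative and may forgo some precision

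*Protocol article*

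**What the plan says.** The matching is stated twice in the protocol article. The abstract (Methods/Design) has: "Both groups will be matched according to gender and type of revision prosthesis". The Study design section repeats it: "The intervention and control groups will be matched according to gender and type of revision prosthesis". Both sentences speak of groups. Neither gives a ratio or a pairing rule.

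The Statistical analysis section says that group differences in rotational, coronal and sagittal alignment "will be determined by using the nonparametric Mann-Whitney U-test for independent samples". For clinical parameters, "t-tests will be used for continuous values or the Mann-Whitney U-test when the variables are not normally distributed". For binary variables, "A Chi-square test and a Fisher’s Exact test will be used for dichotomous values". The threshold is "a p-value of < .05 will be considered to indicate statistical significance". No paired, stratified or covariate-adjusted comparison is named.

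The Sample size section works with two independent proportions without an outlier: "P1 = 0.95, P2 = 0.75, power = 80% and alpha = 0.05, 44 patients per group are needed".

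**The concern.** Matching on a factor that predicts the outcome makes the two groups more alike than two independent samples would be. The difference between groups then varies less than an independent-samples test assumes. Such a test leaves the shared variation in its error term, so its p-values are somewhat too large.

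The article gives a reason to expect that one factor matters. Under Surgical procedure rTKA, the implant model follows the bone-defect type, and the articulating surface follows the state of the collateral ligaments. The Background says that bone loss makes correct positioning harder. Prosthesis type is therefore a marker of what the authors believe makes alignment difficult. For gender the article offers no such link.

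What is at stake is precision in a study of 88 patients (2 × 44). The plan takes the trouble to match and then does not use the matching factors.

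**Working it through.** **1. The plan's own figure.** Inputs from the Sample size section: 0.95 and 0.75, power 80%, alpha 0.05 (taken as two-sided; the article does not say). The arcsine formula for two independent proportions is n = 2(z_α + z_β)²/h², with h = 2(asin√0.95 − asin√0.75) = 0.596.

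n = 2 × (1.960 + 0.842)² / 0.596² = 44.17, which matches the stated 44. The formula is for independent groups, so no gain from matching was built into the sample size.

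**2. Size and power of the unmatched test, by formula.** Let r be the correlation induced by the matching factors (assumed). The true variance of the difference is (1 − r) times the variance that the test assumes. With 1.96 for the critical value and 2.80 for the standardised effect at 80% power:
- size = 2[1 − Φ(1.96/√(1−r))]
- power, unmatched test = Φ((2.80 − 1.96)/√(1−r))
- power, matched analysis = Φ(2.80/√(1−r) − 1.96)

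| r | size | unmatched power | matched power |
|---|---|---|---|
| 0.1 | 3.9% | 81% | 84% |
| 0.2 | 2.8% | 83% | 88% |
| 0.3 | 1.9% | 84% | 92% |

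**3. The same by simulation, including weak factors.** Assumptions, none from the article: 44 per group; normal outcome with total SD 1; two binary factors (prevalence 60% and 30%) with identical distribution in both groups, each carrying half of the explained variance; a 0.6 SD shift for power. Mann-Whitney had 20,000 runs and the matched comparator, Wilcoxon signed-rank, 5,000.

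| variance explained | Mann-Whitney size | Mann-Whitney power | signed-rank power |
|---|---|---|---|
| 0% | 4.9% | 77.3% | 76.4% |
| 2% | 4.9% | 76.9% | 77.2% |
| 5% | 4.5% | 77.6% | 78.5% |
| 10% | 3.7% | 77.9% | 81.5% |
| 20% | 2.9% | 79.4% | 85.7% |
| 30% | 2.0% | 80.6% | 89.4% |

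The simulation error of the signed-rank power is about √(0.8 × 0.2/5000) = 0.6 points, so the differences in the first three rows are close to noise. Power forgone is 81.5 − 77.9 = 3.6 points at 10%, 6.3 at 20% and 8.8 at 30%. The Mann-Whitney columns do not depend on pairing. They hold equally if the groups are only balanced on the two factors.

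**4. Would McNemar be better for outliers?** Outlier rates are 5% and 25% (1 − 0.95 and 1 − 0.75). With within-pair correlation φ (assumed), the probability that both knees are outliers is p11 = 0.0125 + φ√(0.05 × 0.95 × 0.25 × 0.75). The discordant share is p_d = 0.30 − 2·p11. Pairs needed = (1.96√p_d + 0.842√(p_d − 0.04))²/0.04. The simulated power is for 44 pairs with uncorrected tests.

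| φ | pairs needed | McNemar, simulated | chi-square, simulated |
|---|---|---|---|
| 0 | 52 | 76% | 80% |
| 0.05 | 50 | 78% | 81% |
| 0.1 | 48 | 81% | 82% |
| 0.2 | 45 | 86% | 83% |
| 0.3 | 41 | 92% | 85% |

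Up to φ = 0.1, McNemar has no more power than the unpaired test, or less. With these margins φ cannot exceed (0.05 − 0.0125)/0.0944 = 0.40. At φ = 0.3, 82% of the outliers in the navigated group would have an outlier as their match. Two coarse factors are unlikely to produce that.

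**The case against.** The strongest case on the other side is that the harm is conditional. No figure in the article shows that gender or prosthesis type predicts alignment error. If together they explain 5% of the variance or less, almost nothing is lost. This stands, and it is why the size is given as a range that starts at zero.

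It can also be said that a condensed article may leave the type of matching, and any adjusted analysis, to a fuller document. That is fair for the missing matching ratio, which is not criticised here. It does not cover the test itself: the article commits to a comparison "by using the nonparametric Mann-Whitney U-test for independent samples", and that choice does not use the factors its own design fixes.

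A reader might infer three stronger things that the documents do not support:
- **That the p-values could produce false positives.** In every scenario examined, the size of the unmatched test is below 5%.
- **That the study is underpowered because matching is ignored.** The 44 per group claimed no benefit from matching, and the power of the unmatched test rises, not falls, as the factors become more prognostic.
- **That a paired test is required.** The wording describes groups balanced on two categorical factors. It does not describe individual pairs.

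**Conclusion.** The mismatch between design and analysis is real and modest. The named tests use neither matching factor. The consequence, if there is one, is conservatism and forgone precision: type I error of about 4.5–4.9% and 0–1 point of power at 0–5% of variance explained, 3.7% and 3–4 points at 10%, and 2–3% and 6–9 points at 20–30%. The planned 80% power stands.

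These sizes rest on assumed variance shares, a normal outcome, exact balance on the two factors and a 0.6 SD shift. They also use signed-rank as the matched comparator, so the gain from a stratified test is taken to be similar and was not separately tabulated.

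**What to change.** In the Statistical analysis section:
- Compare alignment with a van Elteren test on absolute deviation from target, stratified by gender and prosthesis type, or with a regression that includes both factors.
- Compare outlier proportions with a Mantel-Haenszel test over the same strata, in exact form if cells are sparse.
- State whether matching is by group or by individual pair. Use Wilcoxon signed-rank only if 1:1 pairs are actually formed, and do not make McNemar the default for outliers.

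The cost is a change of wording and slightly more analysis work. Prosthesis type is already on the list of recorded variables under Study procedures, and gender must be known for the matching, so no new data are needed. If the factors turn out not to be prognostic, the loss of power from stratifying is small.

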**Discussion:**

Proper implant position is essential, since malposition leads to worse clinical outcome. Several studies show a significantly positive influence of CAS on prosthetic alignment in primary TKA, but literature about the use of CAS in rTKA is limited. The purpose of this study is thus to investigate the influence of CAS during rTKA on postoperative prosthetic alignment, compared to mechanical navigation guides.

**Trial registration:**

Netherlands National Trial Register NTR3512

## Background

Osteoarthritis (OA) is one of the most prevalent age-related musculoskeletal conditions. Although OA may affect any joint of the body, it is most commonly seen in the hip and knee [1]. OA of the knee leads to a significant impairment in patients’ ability to perform activities of daily living and has a large impact on health-related quality of life [2,3]. For advanced OA of the knee, total knee arthroplasty (TKA) is a highly successful and widely applied surgical treatment, with 450,000 primary TKAs performed in the United States in 2005 [4] and 21,475 TKAs in the Netherlands in 2010 [5]. Due to a growing elderly population and changing thresholds for surgery, these numbers are expected to increase dramatically in the coming decades [4,6].

As a result, the number of TKA revisions (rTKA) will also increase. The demand for rTKA is expected to double by 2015 and a growth of 601% is predicted for the United States between 2005 and 2030 [7]. A similar trend is expected for other Western countries. Main reason for rTKA is aseptic loosening, which accounts for 30-42% of all rTKAs. Infection is the second most common indication and is responsible for about 20% of all revisions. Other reasons for rTKA may be pain, instability, wear, fracture, malalignment, implant breakage, incorrect size and dislocation of one or more components [8,9]. Main reasons for rerevision after rTKA are infection (35-46%), followed by aseptic loosening (19-30%). Other reasons for rerevision are wear/osteolysis, instability, stiffness and periprosthetic fractures [10,11].

The goal of both primary and revision TKA is to restore function and stability of the knee joint and to alleviate pain. However, rTKA is a more complicated surgical procedure than primary TKA and leads to worse clinical results. Major differences between revision and primary TKA are the amount of bone loss and ligamental damage [12,13]. Reasons for this are osteolytic lesions caused by wear, aseptic loosening or infection, and removal of the primary implant.

Proper positioning of the implant is important, since malpositioning of a knee prosthesis leads to worse patient outcome and wear of the prosthesis [14]. Optimal prosthetic alignment is therefore an essential part of the surgical procedure. In primary TKA, one can identify anatomical landmarks and use them to determine the position of the implant using mechanical navigation guides. However, in rTKA most of the time anatomical landmarks have disappeared because of extensive bone loss, making it more difficult to adequately implant the prosthesis.

Several computer navigation systems have been developed to improve prosthetic alignment. In primary TKA, computer-assisted surgery (CAS) is shown to lead to better prosthetic alignment than mechanical alignment guides [15-23]. Several studies have shown improved postoperative mechanical axis as well as coronal, sagittal and rotational prosthetic alignment when using CAS during primary TKA [15,16,24]. Perlick et al. [25] revealed a significantly better mechanical limb axis and coronal alignment of the femoral component when CAS was used during rTKA. However, literature about the use of CAS in rTKA is scarce [25,26] and potential differences in rotational alignment of the prosthesis have not yet been investigated. It is hypothesized that CAS also results in a more accurate prosthetic alignment when used in rTKA. Correct alignment of the prosthesis is more difficult during rTKA compared to primary TKA because of extensive bone loss and the disappearance of anatomical landmarks. This may imply that one can expect more advantages from CAS in rTKA than from primary TKA.

Hence the primary objective of this study was to investigate the effect of CAS on rotational prosthetic alignment when used in rTKA. The effect of CAS on prosthetic alignment in the coronal and sagittal planes will also be determined.

## Methods/Design

### Study design

A prospective clinical intervention study with use of a historical control group will be conducted. In the prospective intervention group patients will undergo rTKA using CAS. These surgeries will take place between September 2012 and September 2015. The historical control group will consist of patients who underwent rTKA between January 2002 and April 2012. The intervention and control groups will be matched according to gender and type of revision prosthesis. The study design, procedures and informed consent are approved by the Medical Ethics Committee of University Medical Center Groningen (UMCG).

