### Study population

The study will be conducted at the Orthopedic Department of UMCG. Inclusion criteria for the intervention group are:

– Use of CAS during rTKA.

– Minimum age of 18 years.

– Total revisions, re-implantations and partial revisions of either the tibial or the femoral part are included. For partial revisions, only measurements of the part of the prosthesis to be revised will be used.

Inclusion criteria for the historical control group are:

– rTKA without the use of CAS.

– Minimum age of 18 years.

– Total revisions, re-implantations and partial revisions of either the tibial or the femoral part are included. For partial revisions, only measurements of the part of the prosthesis that was revised will be used.

– Patients will be included if the NexGen® revision system (Zimmer Inc., Warsaw, Indiana, USA) was used.

Exclusion criteria for both groups are:

– Insert replacements and placement of a patellar button only.

– Patients who receive a tumor prosthesis during rTKA.

– Patients with a limited knowledge of the Dutch language or who are mentally incapable of participating.

In both the intervention group and the historical control group the anesthetic, analgesic and postoperative physiotherapy protocols are identical.

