### Intervention group

In the intervention group, CAS will be applied during rTKA. The ORTHOsoft Navitrack® navigation system (Zimmer Inc., Warsaw, Indiana, USA) will be used. The navigation is based on an infrared reflecting system with use of trackers in the femur and tibia. The system guides the surgery by an image-free model based on anatomical landmarks identified by the surgeon. After the exposure a femoral tracker is placed proximally from the knee in the same knee wound or in an additional 3-cm incision. The tibial tracker will be placed in an additional 3-cm incision above the ankle. Before removal of the primary prosthesis, the navigation protocol is applied in which the anatomical landmarks are chosen and the system will build its model from the patient’s data. Thus, all anatomical landmarks are identified with the primary prosthesis in situ. The mechanical axis of the lower limb as measured with this system is the angle between the mechanical axis of the femur and tibia. The mechanical axis of the femur is the axis between the center of the femoral head and the deepest point of the intercondylar notch. The center of the femoral head is determined by moving the leg in a conical pattern, digitizing 14 distinct positions of the femoral tracker. The deepest point of the intercondylar notch is marked by the orthopedic surgeon. The mechanical axis of the tibia is the axis between the entry point of the proximal medullary canal and the center of the ankle. The entry point of the medullary canal is marked by the orthopaedic surgeon and the center of the ankle is assessed by marking the medial and lateral malleoli. Coronal and sagittal prosthesis alignment of the femoral and tibial components are calculated according to respectively the femoral and tibial mechanical axis. Rotation of the femoral component is determined according to the epicondylar axis. The orthopaedic surgeon marks the medial and lateral epicondyle and thus this axis is generated. Rotation of the tibial component is assessed in relation to the axis between the middle of the posterior cruciate ligament insertion and the medial third of the tibial tuberosity. Both landmarks are marked by the orthopaedic surgeon. The navigation system will guide the surgery in positioning the components and choosing the size of the implants.

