### Study procedures

Demographic characteristics, BMI, indication for operation, type and brand of prosthesis, total amount of blood loss, surgical time, length of hospital stay and ASA classification will be collected and/or recorded for all patients included in this study.

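### The CAS versus historical-control comparison is matched on two factors and tested unadjusted, so residual confounding by indication and revision type, of unknown size and direction, can enter the CAS effect

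*Protocol article*

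**What the plan says.** The Study design section of the protocol article sets the comparison: "A prospective clinical intervention study with use of a historical control group will be conducted". On the intervention group it says: "These surgeries will take place between September 2012 and September 2015". On the controls: "The historical control group will consist of patients who underwent rTKA between January 2002 and April 2012". The periods do not overlap. On comparability: "The intervention and control groups will be matched according to gender and type of revision prosthesis". No other matching factor is named.

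The Study population section applies the same line to both groups: "Total revisions, re-implantations and partial revisions of either the tibial or the femoral part are included". It sets no limit on the mix, and a partial revision contributes only the revised component.

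Under Study procedures, the recorded data begin with: "Demographic characteristics, BMI, indication for operation, type and brand of prosthesis". No role in the alignment comparison is given to them.

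The Statistical analysis section compares rotational, coronal and sagittal alignment by the Mann-Whitney U-test for independent samples. For binary variables: "A Chi-square test and a Fisher’s Exact test will be used for dichotomous values". No regression, stratification or matched-pair method is named.

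The Intervention group section says of navigation: "Thus, all anatomical landmarks are identified with the primary prosthesis in situ".

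**The concern.** In a non-randomised, non-concurrent comparison, the analysis must deal with differences in case mix. Here two factors are matched and the named tests adjust for nothing. The matching itself is not carried into the analysis either, since the groups are tested as independent samples.

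The article supplies the reason to worry. Its Background attributes the bone loss and ligament damage seen in revision to osteolysis from wear, loosening or infection and to removal of the implant. It then says that bone loss and lost landmarks make correct alignment harder. Indication and revision type therefore plausibly bear on the primary outcome, and neither is matched or adjusted for. If their mix shifted between the two periods, part of the observed CAS effect would be case mix. The bias could run either way, exaggerating or hiding a benefit.

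This is not a detail left to a fuller plan. The article names both the matching factors and the test for the primary outcome, and both are stated choices.

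**Working it through.** **1. The plan's own figure.** Inputs (Sample size section): non-outlier proportions 0.95 and 0.75, power 80%, alpha 0.05, 44 per group. The two-sided arcsine formula is n = 2(z₀.₉₇₅ + z₀.₈₀)²/h², with h = 2·asin√0.95 − 2·asin√0.75 = 0.596. It gives 2 × (1.960 + 0.842)²/0.596² ≈ 44.2, which agrees with 44. The formula assumes two exchangeable groups and makes no allowance for confounding. The point made here does not depend on the sample size.

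**2. What is and is not controlled.**

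| Factor | Link to alignment in the article | Matched | In the named test |
|---|---|---|---|
| Bone defect | Direct (Background) | Partly: LCCK or RHK follows defect grade (Surgical procedure) | No |
| Indication | Through bone loss (Background) | No | No, but recorded |
| Revision type | Implant removal as a cause of bone loss (Background) | No | No |
| Period | None stated | Not possible | Cannot be separated from group |

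**3. How much could imbalance do?** The article gives no outlier rates by case type and no case-mix shares, so every input in this step is an assumption. Suppose CAS has no effect and an unmatched factor divides knees into easier and harder cases. Each group's outlier rate is r_easy + (r_hard − r_easy) × share of harder cases. The last column is the two-sided normal-approximation rejection rate for two proportions with 44 per group.

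| Outlier rate, easy / hard | Harder share, control / CAS | Control rate | CAS rate | Spurious difference | Rejection |
|---|---|---|---|---|---|
| 15% / 35% | 50% / 50% | 25% | 25% | 0 points | 5% |
| 15% / 35% | 60% / 40% | 27% | 23% | 4 points | 7% |
| 10% / 40% | 70% / 30% | 31% | 19% | 12 points | 25% |
| 5% / 45% | 70% / 30% | 33% | 17% | 16 points | 41% |

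For example, in the third row, control = 0.10 + 0.30 × 0.70 = 0.31 and CAS = 0.10 + 0.30 × 0.30 = 0.19. Reversing the shares reverses the sign. The figures concern the binary outlier endpoint and only illustrate what could happen to the Mann-Whitney comparison of angles.

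**4. What an adjusted model can carry.** Expected outliers under the plan's rates are 44 × 0.25 + 44 × 0.05 = 11 + 2.2 = 13.2. That supports one or two covariates in an ordinary logistic model. A linear model of a continuous deviation carries more. Group, gender, prosthesis type (taken as two levels), revision type, indication and BMI make six coefficients plus an intercept. If all 88 knees contribute, 88 − 7 = 81 residual degrees of freedom remain. Partial revisions of the other component reduce that number.

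**5. Why not simply match on more.** Four revision types × two genders × two prosthesis types = 16 cells, or 44/16 = 2.75 CAS knees per cell on average. The pool of 165 control-period procedures is stated without saying that eligibility was applied, and controls must still return for a CT scan.

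**6. Re-implantations.** Study population lists them separately from total revisions and makes them eligible. The Intervention group section describes landmark registration before the primary prosthesis is removed. If a re-implantation follows an earlier removal, both statements cannot hold for that knee. The article does not define the term.

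**The case against.** The strongest reply is that the design already controls the main pathway. Alignment difficulty runs through bone loss, prosthesis type follows defect grade, and prosthesis type is matched. The study is at one centre with one revision system, and the article says both groups used the same anatomical landmarks. This stands in part: only prognostic differences remaining after the matching can bias the result. But prosthesis type is an indirect proxy and captures neither indication nor revision type.

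A second reply is that a condensed article leaves covariate adjustment to the full plan. That would hold if the article were silent, but it names an unadjusted test for the primary outcome. It is fair, however, that the recorded covariates are not said to be purely descriptive: the article also plans between-group tests of clinical parameters.

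Three stronger readings are tempting and unsupported:

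- A reader might infer that case mix could account for the whole planned difference. None of the scenarios tried reached 20 points, even with severe assumed inputs.
- A reader might infer that partial revisions have fewer outliers mechanically, because fewer components are scored. The Radiographic evaluation section measures femoral and tibial rotation separately, so component by component no such advantage arises.
- A reader might convert the background share of revisions due to infection into a count of CAS knees that do not fit the navigation description. The article nowhere equates infection with re-implantation.

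**Conclusion.** The concern holds as a weakness of the stated analysis, not as a demonstrated bias. The article fixes a non-concurrent comparison matched on two factors and tested without adjustment, and its own reasoning makes indication and revision type plausible confounders. The size and direction of any bias cannot be computed from the document. The 4-to-16-point range rests entirely on assumed outlier rates and case-mix shares, and shows only that moderate to severe imbalance can inflate the false-positive rate and supply part of the expected effect.

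Adjustment would reduce this but not cure the design. Calendar period is fully aliased with group, so changes in era or surgical experience stay in the estimate under any model. The wording on re-implantations is a separate ambiguity about what some CAS patients received. It is a real inconsistency if the term means implantation after an earlier removal.

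**What to change.** 1. Keep the planned matching. For each component (femoral, tibial), make the main estimate a regression of absolute deviation from the stated target on group. Adjust for gender, prosthesis type and a short prespecified set: total versus partial revision, infection versus other indication, and BMI. Use the two-level revision term, because a finer one fails in component-specific models: a tibial-only revision has no femoral value, and the reverse. State beforehand how re-implantations are coded. Do not add a separate re-implantation term, since it is likely to be collinear with infection.
2. Report the unadjusted Mann-Whitney result as supportive.
3. Limit any adjusted model of the binary outlier endpoint to one or two covariates, or use a penalised fit.
4. State that period effects cannot be adjusted away, and word the conclusion accordingly.
5. Reconcile the eligibility of re-implantations with the description of landmark registration, and report the effect with and without these knees.

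The cost is small: revised analysis wording, slightly more analysis work and a few degrees of freedom. Indication, BMI and prosthesis type are already recorded, and revision type must be known to apply the plan's own rule on partial revisions.
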